# List of used abbreviations

MPA Medical Products Agency

SmPC Summary of Product Characteristics

CRF Case Record forms

IMP Investigational medical product

AE Adverse event

SAR Serious adverse event

SUSAR Suspected unexpected adverse event

# Summary

*Clostridium difficile* is an opportunistic pathogen that causes diarrhoea and colitis and is associated with a 2.5 fold increased mortality risk. Infection typically arises following destruction of the intestinal bacterial composition (microbiota) by antibiotic treatment. Patients at risk of *C. difficile* infection can be identified through risk factors such as age and planned antibiotic exposure during e.g. planned medical interventions. *C. difficile* infection is typically treated with antibiotics. However, infection recurs in up to 30% of patients after a first episode and in up to 60% after two or more recurrences. Recurrent infections are most effectively treated by inoculating the diseased gut with bacteria from a donor (faecal microbiota transplantation). Faecal transplantation is typically a prolonged process involving family members, extensive screening and optimally gastroscopy or colonoscopy. Filtered and concentrated stool samples from unrelated donors put into capsules and frozen have recently been shown to be safe and efficacious. This study aims to assess the safety and tolerability of capsules containing autologous microbiota compared to placebo in healthy volunteers after antibiotic exposure. The time to recovery of intestinal microbiota will be determined using the next generation sequencing platform developed by Science for Life Laboratory. The long-term aim is to establish a method whereby patients can leave a stool samples prior to planned antibiotic exposure that can be used prophylactically to reconstitute intestinal microbiota whereby the risk of *C. difficile* infection is minimised and to enable rapid treatment of patients needing a faecal transplant.

# 1 BACKGROUND

*Clostridium difficile* is a toxin producing bacillus and an opportunistic pathogen that causes diarrhoea and colitis. *Clostridium difficile* infection (CDI) is a common and increasingly severe, primarily nosocomial infectious disease associated with a 2.5 fold increased 30 day mortality ([1](#_ENREF_1), [2](#_ENREF_2)). In the US there were an estimated 453 000 cases and 29 300 deaths in 2011 ([3](#_ENREF_3)). Swedish laboratories reported ~9575 episodes of CDI in Sweden in 2015 ([4](#_ENREF_4)). CDI usually occurs following antibiotic mediated destruction of the intestinal bacterial composition (microbiota) and can occur several weeks after antibiotic treatment. In line with this, the most pronounced disruption of the intestinal microbiota was during the 1^st^ month but changes lasted for at least 12 months in healthy volunteers taking clindamycin for 10 days ([5](#_ENREF_5)). Other risk factors for CDI include hospital admission, advancing age and severe underlying disease ([6](#_ENREF_6)).

A first episode of CDI is treated with metronidazole or vancomycin for 10 days. However, CDI recurs in up to 30% of patients after a first episode and in up to 60% after two or more recurrences ([7](#_ENREF_7), [8](#_ENREF_8)). The concept of treating CDI with additional antibiotics instead of reconstituting the gut flora has recently been challenged. Faecal microbiota transplantation and vancomycin treatment cured 81-94% and 23-31% of patients, respectively in a ground breaking randomised clinical trial in patients with recurrent CDI ([9](#_ENREF_9)). The effectiveness of inoculating microbiota for treatment of recurrent CDI has since been confirmed ([10-13](#_ENREF_10)). In line with this, we achieve approximately 90% treatment success when faecal microbiota transplantation, given as an enema, is used in routine clinical practice for treatment of recurrent CDI at Danderyds hospital (unpublished data). In essence faecal microbiota transplantation results in reconstitution of the normal intestinal microbiota by inoculation of a healthy individual’s microbiota into the diseased gut.

For faecal microbiota transplantation, a suitable relative is typically found and screened for various infectious entities. A fresh stool sample is collected from the donor and introduced to the patient’s intestine through a rectal enema, colonoscopy, nasogastric tube or gastroscopy. Identifying and screening takes days, enemas require that diarrhoea has been suppressed, obtaining a gastroscopy often takes time and there is a risk of regurgitation. The process thus takes time, is costly and potentially disgusting and needs to be improved.

Recent studies have shown that stools from unrelated healthy donors are as effective as stools from related donors ([14](#_ENREF_14)). Frozen stools are as effective as fresh and a preliminary feasibility study found that oral, capsulized frozen faecal microbiota transplantation cured 90% (18/20) patients with recurrent CDI ([12](#_ENREF_12), [13](#_ENREF_13)).

Antibiotic mediated destruction of the intestinal microbiota results in loss of colonization resistance not only against *C. difficile*. Drug resistant bacteria can also expand resulting in dense colonization ([15](#_ENREF_15), [16](#_ENREF_16)). This increases the risk of resistance transmission and of bacteria crossing the intestinal membranes (translocation) resulting in deep tissue and bloodstream infection ([15-17](#_ENREF_15)). Faecal microbiota transplantation rapidly reduced bacterial translocation and the presence of carbapenem resistant klebsiella in mice that had been treated with ampicillin and were infected with carbapenem resistant klebsiella ([16](#_ENREF_16)).

Replacing the donor with autologous faeces would circumvent the difficulty of finding a suitable donor and screening. Furthermore, an autologous transplant could be given prophylactically after planned antibiotic exposure such as a surgical procedure. Prophylactic reconstitution of intestinal microbiota may also reduce the risk of multidrug resistant bacteria causing infection. We therefore plan to determine the safety and tolerability of oral, capsulized, frozen autologous faecal microbiota inoculation in healthy volunteers after antibiotic treatment. The time to reconstitution of the intestinal microbiota will be assessed using the Clinical Genomics platform at the Science for Life Laboratory ([www.scilifelab.se](http://www.scilifelab.se)). This is a large scale throughput next generation sequencing based platform for the analysis of intestinal microbiota. The bacterial composition is determined by analysis of bacterial 16S rRNA gene that contains stable regions, suitable for primers and variable regions, suitable for species differentiation. More than 2000 samples have been successfully amplified using this platform and its coupled bioinformatics.

# 2. RATIONALE

Restoration of the intestinal microbiota by oral, capsulized, frozen, faecal microbiota inoculation has been shown to rapidly cure recurrent CDI. However, inoculation of donated microbiota requires extensive screening and may inoculate unwanted pathogens. Patients at high risk of *C. difficile* infection can be identified prior to planned medical procedures that further increase the risk. The long term aim of this project is to enable such patients to store faecal material for future autologous microbiota inoculation. This study specifically aims to determine the tolerability and safety of enteric resistant capsules that can be used for home based autologous microbiota inoculation. We plan to use clindamycin to disrupt the intestinal as previous data has shown the pronounced effect this drug has whilst it is also a safe commonly used and well tolerated antibiotic. Moreover, clindamycin treatment of healthy volunteers was approved by the regional ethical board in Stockholm for a study published in 2015 on the long-term effect of antibiotic administration on the human normal intestinal microbiota. The amount of bacteria in a given amount of stool varies manifold and for that reason it has not been possible to determine the dose of bacteria required to restore the intestinal microbiota. In clinical practice two spoons of faeces given as an enema typically resolve CDI. In a clinical trial 15 capsules given once daily for two days and repeated in case symptoms didn’t resolve also resolved CDI. However, giving 15 capsules in one go is not clinically practical. The proposed dosing is thus a manageable two capsules twice daily for five days which is likely to deliver a similar total amount of bacteria as the above dosing schedules.

# 3. Cost benefit assessment

The risk posed to participants are primarily allergic reactions to the antibiotic used (clindamycin) and antibiotic associated diarrhoeal disease, particularly CDI, caused by clindamycin. Clindamycin is well tolerated and rarely causes allergic reactions and the optimal treatment of CDI is inoculation with healthy intestinal microbiota which half the study participants will receive and all can do in case CDI develops. Moreover, study participants are screened for *C. difficle* prior to study entry so the risk of CDI is very low. Inoculation with intestinal microbiota has in repeated trials been shown to be well tolerated and our clinical experience is also that this treatment is well tolerated. Should anyone accidentally bite the capsule this will be disgusting but not hazardous to health. Theoretically a participant might vomit and the inhale the contents of the capsules. This is likely to cause a severe pneumonia. However, participants are healthy volunteers and the number of tablets taken at each time point is small. The risk of aspiration pneumonia is therefore exceedingly small. The potential benefit of this treatment is to develop a rapidly available treatment for CDI and for prevention of CDI, a disease that causes considerable morbidity and mortality and for which current treatment regimens are either suboptimal or very cumbersome. The benefits therefore considerably outweigh the potential risks.

#

# 4. AIM

To determine the safety and tolerability of oral, capsulized, previously frozen, autologous faecal microbiota transplantation up to 21 days after the end of faecal treatment in healthy volunteers.

# 5. Outcomes

## 5.1 Primary endpoint

The safety and tolerability of oral, capsulized, previously frozen, autologous faecal microbiota transplantation up to 21 days after the end of faecal treatment in healthy volunteers.

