## 6.9 Treatment

Participants will come to the Department of Infectious Diseases, Danderyds hospital or Mälarsjukhuset in Eskilstuna the day prior to treatment start to collect clindamycin and for a final briefing. All participants will be requested to take 300 mg clindamycin capsules morning, lunch and evening for seven days. This will be followed by a two and a half day washout period. On day three of the washout period participants will return to Hospital to take the first IMP or placebo dose supervised and to collect their remaining study capsules that are to be stored in a freezer at home. Participants will then be requested to take two study capsules twice daily for a total of five days.

An SMS text message will be sent twice daily to remind volunteers to take the clindamycin and study capsules. Patients and investigators will be blinded as to the content of the capsules. The code will be held by the manufacturers of the capsules that are not involved in the clinical part of the study.

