## 6.10 Monitoring and follow up:

Upon inclusion clinical records form (appendix A) will be completed.

Stool habits and characteristics will be monitored daily from treatment start until day 28 and at 2 and 6 months using the structured questionnaire in appendix B. Questionnaires record stool frequency and consistency, general and gastrointestinal well-being via a standardized health score, rating of gastrointestinal symptoms and medication use. Overall and gastrointestinal-specific health scores will be reported on a scale of 1 to 10, with 1 being the lowest and 10 being “best possible health for you.”

Stool samples for sequencing will be taken at baseline and on days 10, 16 (+3 days if necessary), 28 and at 2 and 6 months.

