**Table 1. Outline of study and sampling**

| Days |  | 1 | 1-7 | 8-10 | 10-15 | 16 | 28 | 2 months | 6 months |
| --- | --- | --- | --- | --- | --- | --- | --- | --- | --- |
| Phase | Inclusion | Start | Antibiotic | Washout | Treat | Follow up | | | |
| CRF A | + |  |  |  |  |  |  |  |  |
| *C.diff* screening | + |  |  |  |  |  |  |  |  |
| Faecal sample* | + | + |  | + |  | + | + | + | + |
| CRF B |  | + | + | + | + | + | + | + | + |
| Hospital visit | + | + |  | + |  | + |  |  |  |

*Prior to study start a faecal sample for autologous transplant will be donated.

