# 7. SAFETY AND ADVERSE EVENTS

## 7.1 Specification of safety parameters

Safety parameters; Adverse drug reactions and serious adverse drug reactions and changes in vital signs.

Any apparent side effects experienced by the subject will be assessed from the time the subject signs the informed consent and throughout the course of the entire study, and will be reported by study site personnel either as a Baseline Event or an AE (6.2). The study personnel will document any Baseline Events or AEs in the CRF, whether observed by the Investigator or reported by the subject. The safety of the different treatment arms will be assessed with regard to AEs, baseline medical conditions, and findings from the physical examination and laboratory tests.

Possible adverse events will be elicited using a modification of the Common Terminology Criteria for Adverse Events version 3.0. as used by Youngster et al ([13](#_ENREF_13), [19](#_ENREF_19)). Fever, gastrointestinal symptoms, headache, fatigue, and rash will be the principle symptoms evaluated (appendix B).

The AE reporting period is described in Section 6.2.

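### Daily symptom recording stops at day 28, about eight days before the 21-day primary safety window closes, so the last part of that window rests on general adverse event reporting and recall

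*Protocol*

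**What the plan says.** Section 5.1 of the Protocol, like the aim in Section 4, sets the period for safety and tolerability as "up to 21 days after the end of faecal treatment in healthy volunteers".

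Section 6.9 gives the sequence that fixes the calendar. For the antibiotic: "All participants will be requested to take 300 mg clindamycin capsules morning, lunch and evening for seven days". Then: "This will be followed by a two and a half day washout period". Then: "On day three of the washout period participants will return to Hospital to take the first IMP or placebo dose supervised". Capsules are then taken twice a day for five days in all. Table 1 puts this on one day axis starting at clindamycin. After the antibiotic column (1-7), the day headings read "8-10 | 10-15 | 16 | 28 | 2 months | 6 months", and 10-15 is the capsule treatment phase.

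On data collection, Section 6.10 says: "Stool habits and characteristics will be monitored daily from treatment start until day 28 and at 2 and 6 months", using the questionnaire in appendix B. Section 7.1 ties the main safety symptoms to that questionnaire: "Fever, gastrointestinal symptoms, headache, fatigue, and rash will be the principle symptoms evaluated (appendix B".

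Adverse events are also collected outside the questionnaire. Sections 7.5 and 7.6 open the reporting period for serious and for all adverse events at capsule administration and close it at a follow-up visit 6 months after the end of the investigational product. Section 7.4 prescribes a question about health problems since the previous evaluation and requires the absence of events to be noted actively.

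**The concern.** The period named in the primary endpoint and the period of daily symptom recording do not match. The appendix B questionnaire is the instrument that the Protocol names for fever, gastrointestinal symptoms, headache, fatigue and rash, and it also carries the general and gastrointestinal health scores. These are mostly mild, subjective complaints. A tolerability claim rests on them, and they are the complaints most easily lost when nobody asks at the time.

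If daily recording ends well before day 21 after treatment, symptom proportions reported for the full window mix two kinds of ascertainment: prompted daily entries at first, then unprompted reports and recall. With 12 participants per arm, one affected participant is 1/12, or 8.3 percentage points, so a few unrecorded complaints would visibly change the proportions that Section 11.3 plans to report. No analysis plan can recover diary days that were never collected.

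**Working it through.** **Inputs**
- Window length: 21 days after the end of capsule treatment (Sections 4 and 5.1).
- Clindamycin: days 1-7 (Section 6.9, Table 1).
- First capsule: day three of a washout that begins on day 8, hence day 10 (Section 6.9, Table 1).
- Capsule course: twice daily for five days, hence 10 intakes (Section 6.9).
- Capsule phase in Table 1: days 10-15.
- Last day of daily questionnaires: day 28 (Section 6.10).

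**Does Table 1 fit Section 6.9?** With a first intake part-way through day 10, the 10 intakes fall as 1 on day 10, 2 on each of days 11-14 (8 in all), and 1 on day 15: 1 + 8 + 1 = 10. Table 1's end on day 15 is reproduced.

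**Main calculation**
- Window closes: 15 + 21 = day 36.
- Post-treatment days with daily recording: 28 − 15 = 13, and 13/21 = 62%.
- Days without it: 36 − 28 = 8 (days 29-36), and 8/21 = 38%.

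**Sensitivity to the day count.** Last capsule day = start + floor((10 − 1 + h)/2), with h = 0 if the first intake is a morning one and h = 1 if it is later in the day.

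| First intake | Last capsule | Window closes | Days recorded daily | Days not |
| --- | --- | --- | --- | --- |
| Day 10, morning | 14 | 35 | 14 | 7 |
| Day 10, later (Table 1) | 15 | 36 | 13 | 8 |
| Day 11, morning | 15 | 36 | 13 | 8 |
| Day 11, later | 16 | 37 | 12 | 9 |

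The shortfall is 7 to 9 days. The last row runs past Table 1's day 15 and serves only as an outer bound.

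**Could day 28 be counted from the first capsule?** It would then be study day 10 + 27 = 37, and the shortfall would vanish. The text does not allow this. Section 6.9 has participants attend on the day before treatment start to collect clindamycin, so treatment start there means the antibiotic. Table 1 has a single axis, with the questionnaire (CRF B) marked from day 1 and day 28 on the same axis as days 10 and 16.

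**What is scheduled in days 29-36?** Table 1 shows nothing between day 28 and 2 months, and no hospital visit after day 16.

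**Length of recall.** The origin of the 2-month contact is not defined, so this is an assumption. At about day 60 from the start of clindamycin, recall of days 29-36 reaches back 60 − 36 = 24 to 60 − 29 = 31 days. Counted as 60 days from the last capsule (day 75), it reaches back 75 − 36 = 39 to 75 − 29 = 46 days.

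**The case against.** The strongest reply is that the endpoint is not the diary. Section 5.1 names no instrument and does not ask for an entry on each of the 21 days. Section 11.3 reports proportions of adverse events, and these also come from general reporting. That reporting covers the whole window (Sections 7.5 and 7.6), Section 7.1 has side effects assessed throughout the study, and the question in Section 7.4 reaches back over days 29-36 when it is next asked. Daily recording does cover the whole intake period and about 13 days after it. Follow-up is identical and blinded in the two arms (Sections 6.6 and 6.9), so the gap itself gives no reason to expect bias between them.

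All of this stands, and it limits the point. A reader might infer that the primary endpoint goes unobserved after day 28, or that the trial would have only 13 days of observation. The documents do not support either reading: what stops is daily, structured symptom collection. Nor can one say that mild events will be missed, only that they may be.

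Two further inferences should be left aside. Day 28 is 21 days after the last clindamycin day (28 − 7 = 21), which might suggest that the window was tied to the wrong treatment. Sections 4 and 5.1 both refer to faecal treatment, and nothing says how day 28 was chosen. Section 7.1 also lists "serious adverse drug reactions and changes in vital signs", with physical examination and laboratory findings, and Table 1 has no row for any of these. That is a separate, minor matter. Table 1 is only an outline, and what the case record forms contain is set out in appendices that are not in the text reviewed.

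The reply does not remove the mismatch. Look-back some weeks later does not replace daily prompting for mild symptoms, and similar under-counting in both arms still lowers the absolute rates and makes a real difference harder to see.

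**Conclusion.** The inconsistency holds, in a limited form. Daily recording of the principal safety symptoms ends at day 28, about 8 days (range 7-9) before the primary window closes at about day 36. Daily structured data cover 13 of the 21 post-treatment days; the rest depends on general adverse event reporting and on look-back at the 2-month contact. The likely consequence is some under-counting of mild symptoms late in the window, probably alike in both arms, so that absolute tolerability rates may be understated. The documents give no symptom rates from which to estimate how many events this would be.

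This rests on Table 1's day axis running from the start of clindamycin and on the capsule course ending on day 14, 15 or 16. No day count on that axis closes the gap. The matter is modest for a 24-person descriptive safety study. It does concern the only primary endpoint, though, and it can be put right only before the data are collected.

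**What to change.** Reconcile Sections 4 and 5.1 with Section 6.10 and Table 1 before enrolment, in one of two ways.

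1. **Preferred:** extend the daily CRF B to the last capsule plus 21 days (about day 36). State this in Section 6.10 and show it in Table 1. Defining the end by the last capsule actually taken, instead of by a fixed study day, would remove the 7-to-9-day ambiguity. The cost is a small amendment and about eight more home questionnaires per participant, with no extra visit.
2. **Otherwise:** restate the primary window in Sections 4 and 5.1 as ending on day 28, about 13 days after the last capsule. This costs no additional data collection, but the tolerability claim is shorter. Later events would still be reported from the general adverse event collection.

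Separately, check the vital signs, physical examination and laboratory items in Section 7.1 against the appendices, and align the text if they are not collected.

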## 5.2 Secondary endpoints

To determine rate at which the composition of intestinal microbiota is normalised through next generation sequencing of stool samples collected for up to six months

To determine the time to normalisation of stool habits

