# 6. METHODS

## 6.1 Study Design

A double blind placebo controlled phase 1 clinical trial conducted at Danderyds Hospital, Danderyd and Mälarsjukhuset, Eskilstuna both in Sweden.

The double blinded placebo controlled study design has been chosen to enable unbiased assessment of adverse events. The study will be conducted in accordance with the Helsinki declaration on ethical principals for medical research involving human subjects.

Twenty-four volunteers will be included in the study. Following informed consent participants will be requested to donate faeces. Participants will be randomised to treatment group A or B. Treatment will consist of clindamycin 300 mg three times daily for seven days for all. This will be followed by intake of two identical capsules twice daily containing placebo or an autologous faecal mixture for five days. Participants general health and gastrointestinal symptoms will be monitored using questionnaires and stool samples for sequencing of the microbiota will be collected. The study will end when the six month follow up of the last patient ends.

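### The protocol promises a time to recovery of the microbiota, but six months of sampling and the stated analysis support only the rate or extent of normalisation up to six months

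*Protocol*

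**What the plan says.** **The promise.** The Summary states: "The time to recovery of intestinal microbiota will be determined using the next generation sequencing platform". Section 1 repeats this as "The time to reconstitution of the intestinal microbiota will be assessed using the Clinical Genomics platform". Section 5.2 words the endpoint differently, as a rate of normalisation, and gives it a six-month limit: "To determine rate at which the composition of intestinal microbiota is normalised through next generation sequencing of stool samples collected for up to six months".

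**The window.** Section 6.10: "Stool samples for sequencing will be taken at baseline and on days 10, 16 (+3 days if necessary), 28 and at 2 and 6 months". Section 6.1 closes the study with the last participant's six-month follow-up.

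**The expected persistence.** Section 1 reports from an earlier clindamycin study that "changes lasted for at least 12 months in healthy volunteers taking clindamycin for 10 days". The same sentence places the greatest disruption in the first month. In this trial the course is shorter (section 6.1): "Treatment will consist of clindamycin 300 mg three times daily for seven days for all".

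**The analysis.** Section 11.3 plans a Shannon index for every sample, tested with the Wilcoxon rank-sum test, and unweighted UniFrac distances used for ordination plots. It names no method for a time to an event. It does not relate a participant's later samples to that participant's own pre-antibiotic sample.

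**The concern.** The Summary and section 1 commit the trial to a quantity that its last sampling day may not allow it to observe. The protocol's single figure on how long clindamycin changes persist is at least twice the sampling window, and no section explains why six months is enough. The last sampling day is fixed in the protocol, and no later analysis can recover a time beyond it.

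At stake is how the microbiota result can be reported. If an appreciable share of participants, especially on placebo, are not back to baseline at six months, the trial can say how far each arm has come by each visit. It may be unable to give a typical recovery time for placebo, and hence a difference in recovery times between arms. The analysis in section 11.3 does not fill the gap, because it compares diversity values and draws plots without measuring return to baseline.

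**Working it through.** **Figure to reproduce.** There is none. Section 11.1 says that no power calculation was done, and the protocol states no recovery-time assumption. The only arithmetic is 12 per arm × 2 = 24, which agrees with section 6.1.

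**Step 1: window against persistence.** Sampling ends at 6 months (sections 5.2 and 6.10). The cited persistence is at least 12 months (section 1). The ratio is at most 6/12 = 0.5.

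**Step 2: how finely a recovery can be dated.** Take 2 months as about day 60 and 6 months as about day 183. Table 1 places the day-10 sample at the end of washout, so four samples follow the capsules.

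| Interval | Width |
| --- | --- |
| day 10 to 16 | 6 days |
| day 16 to 28 | 12 days |
| day 28 to 2 months | 60 − 28 = 32 days |
| 2 to 6 months | 183 − 60 = 123 days |

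If the three-day allowance at day 16 is used, the first two widths become 9 and 9 days. The last interval, about 4 months, needs no assumption about recovery.

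**Step 3: share not recovered at six months (illustration).** The documents give no recovery distribution. Assume exponential recovery with median m months, for the 12 placebo participants:

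- share recovered by 6 months: p = 1 − 2^(−6/m)
- expected number recovered: 12p
- chance that at least half are seen to recover, so that a median can be estimated: the sum over k = 6 to 12 of C(12,k) p^k (1−p)^(12−k)

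For m = 12: p = 1 − 2^(−0.5) = 0.293, 12p = 3.5, and the binomial sum is 0.11.

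| Assumed median (months) | Not recovered at 6 months | Expected recovered of 12 | Chance that at least 6 of 12 recover |
| --- | --- | --- | --- |
| 3 | 25% | 9.0 | 0.99 |
| 6 | 50% | 6.0 | 0.61 |
| 9 | 63% | 4.4 | 0.26 |
| 12 | 71% | 3.5 | 0.11 |
| 18 | 79% | 2.5 | 0.02 |
| 24 | 84% | 1.9 | 0.01 |

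The last column runs from almost certain to almost impossible. The table shows that the feasibility of a placebo recovery time depends on an input that the protocol does not supply. It does not show which row applies.

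**Step 4: what section 11.3 delivers.** A rank-sum test on Shannon indices compares diversity between groups of samples. An ordination of UniFrac distances displays similarity. Neither produces a time, and neither is set up as a change from the participant's own baseline, although the samples allow it.

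**The case against.** The strongest reply is that the endpoint itself is sound. Section 5.2 asks for a rate and states its own six-month horizon. A rate or trajectory can be estimated from a baseline and five later samples without anyone recovering fully. Section 1 puts the greatest disruption in the first month, where the sampling is densest. Time to recovery appears only in narrative text, in a phase 1 study whose aim is safety and tolerability. All of this stands, and it confines the point to the wording of the claim and the choice of measure.

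A reader might infer more, in four ways that the documents do not support.

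- *Placebo recovery is expected to fall outside the window, so 0 of 12 times would be seen.* The 12-month figure describes a group after 10 days of clindamycin; this trial gives 7. It does not say which measure changed or in how many people. Many individuals, or the Shannon index, could be back at baseline by six months.
- *The trial cannot give a rate.* It can, up to six months.
- *The analysis will average times among those who recover and so lose the slowest.* No section plans this.
- *The trial sets out to show that the capsules shorten recovery.* No such hypothesis or endpoint is stated.

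A definition of normalised and rules for censoring may properly sit in a statistical analysis plan that is not shown. Their absence here is not a fault in itself.

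**Conclusion.** The point holds in a limited form. The Summary and section 1 promise a time to recovery or reconstitution that the six-month window may not capture and that the stated analysis does not estimate. The mismatch between this promise and the protocol's own persistence figure is not addressed anywhere in it.

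The number of recovery times that would be missed is unknown. It depends on the recovery distribution after a 7-day course and on how normalised is defined, and the documents give neither. The range in the working rests on an assumed exponential shape and assumed medians. Only the roughly four-month uncertainty between months 2 and 6 follows from the schedule itself. Early and partial recovery, and differences between arms at fixed visits, remain measurable. This is a secondary endpoint of an unpowered safety study, and the primary endpoint is untouched, so the correction is worthwhile but modest.

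**What to change.** - **Summary and section 1:** replace time to recovery or reconstitution with the rate or extent of normalisation up to six months.
- **Sections 5.2 and 11.3:** make the measure each participant's distance from the pre-antibiotic sample (for example the UniFrac distance, together with the change in Shannon index) at days 10, 16 and 28 and at 2 and 6 months. Compare the arms at the post-capsule visits, day 16 onwards. Keep day 16, because it is the first sample after the capsules and lies in the month of greatest disruption.
- **Add the proportion back to baseline by six months.** The criterion for being back should be set before unblinding; it may be placed in the statistical analysis plan.
- **Participants not back at six months** count as not recovered and are not dropped. If a recovery time is reported as well, treat it as interval-censored between visits and right-censored at the last sample.

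The cost is wording in four places and slightly more analysis. No new samples or visits are needed. The downside is a less ambitious claim than a time to recovery.
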